## Secondary outcomes

### Prevalence outcomes

The prevalence of malaria infection among participants aged 6 months and older, detected by RDT, will be analyzed using a multi-level (variance components model) constructed on a generalized linear model framework with a Bernoulli likelihood and a logit link function. Random intercepts will be included for each study cluster, and the study arm will be included as a fixed effect coded categorically as 0 for arm A and 1 for arm B. The analyst will be blinded to the true assignment until the results are presented. The model will take the form below where *p*_*ij*_ is the probability of positivity at the individual level (*i* indexes individuals within clusters and* j* indexes clusters), *α* is the global intercept, *X*_ij_ is the arm assignment for individual *i* in cluster *j*, *β*_*arm*_ is the arm effect to be estimated, *u*_*j*_ are random intercepts for the cluster, and *σ* is the standard deviation of the random intercept distribution:$$\mathrm{logit}({p}_{ij})=\alpha +{X}_{ij}^{arm}{\beta }_{arm}+{u}_{j}$$where the likelihood is of the form:$${y}_{ij}\sim Bernoulli({ p}_{ij})$$

And the random intercepts are assumed to follow a normal distribution:$${u}_{j}\sim N(0,{\sigma }^{2})$$

Model results will be presented as the estimates of *e*^*α*^ and the odds ratio above and the standard deviation or variance of the random effects distribution. 95% confidence intervals for the odds ratio and *e*^*α*^ estimates as well as *z*-statistics and *p*-values for each coefficient will be presented.

### Routine clinical incidence

The incidence of clinical malaria obtained from passive case detection will be analyzed as total incidence using a generalized linear model framework with a Poisson likelihood and a log link function. The incidence will be summed for all months of follow-up within each study cluster, and the study arm will be included as a fixed effect coded categorically as 0 for arm A and 1 for arm B. Exposure will be the population of the cluster as assessed during enumeration. The analyst will be blinded to the true assignment until the results are presented. The model will take the form below where *y*_*i*_ is the total incidence at the cluster level where only aggregated data is available (*i* indexes clusters), *α* is the global intercept, *X*_i_ is the arm assignment for cluster *i*, *β*_*arm*_ is the arm effect to be estimated, *exposure*_*i*_ is the person time at risk for cluster *i*, and *λ*_*ij*_ refers to the *log E(y*_*ij*_*|u*_*j*_*).*:$$\mathrm{log}E({y}_{i})=\alpha +{X}_{i}^{arm}{\beta }_{arm}+\mathrm{log}({exposure}_{i})$$

where the likelihood is of the form:$${y}_{i}\sim Pois({\lambda }_{ij})$$

Model results will be presented as the estimates of $${e}^{\alpha }$$ and incidence rate ratios above and the standard deviation or variance of the random effects distribution. 95% confidence intervals for the IRR and $${e}^{\alpha }$$ estimates as well as *z-*statistics and *p*-values for each coefficient will be presented. Results will be presented as incidence rates and incidence rate ratios along with their associated 95% confidence intervals, and *p*-values.

The outcome will also be checked for the distributional assumption that the mean and variance of the outcome are similar after conditioning on a cluster (e.g., are the within-cluster mean and variance similar); if the variance is substantially larger, a negative binomial likelihood will be considered.

Where individual-level data is available for this outcome, a similar approach will be followed but instead focused on cumulative incidence and using a variance components model. The model will take the form below where *y*_*ij*_ is incidence at the individual (*i* indexes individuals within clusters and* j* indexes clusters), *α* is the global intercept, X_ij_ is the arm assignment for individual *i* in cluster *j*, *β*_*arm*_ is the arm effect to be estimated, *u*_*j*_ are random intercepts for the cluster and *exposure*_*i*j_ is the person time at risk for individual *i* in cluster *j*, *λ*_*ij*_ refers to the *log E(y*_*ij*_*|u*_*j*_*)*, and *σ* is the standard deviation of the random intercept distribution:$$\mathrm{log}E\left({y}_{ij}|{u}_{j}\right)=\alpha +{X}_{ij}^{arm}{\beta }_{arm}+{u}_{j}+\mathrm{log}({exposure}_{ij})$$

where the likelihood is of the form:$${y}_{ij}\sim Pois({\lambda }_{ij})$$

And the random intercepts are assumed to follow a normal distribution:$${u}_{j}\sim N(0,{\sigma }^{2})$$

Results will be presented as the incidence rate ratio (IRR), corresponding 95% confidence interval, and *p*-value based on the *z*-statistic. The primary outcome will also be checked for the distributional assumption that the mean and variance of the outcome are similar after conditioning on a cluster (e.g., are the within-cluster mean and variance similar) and if variance is substantially larger a negative binomial likelihood will be considered.

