### Passive case detection

Data from all health facilities regarding people of all ages will be used to calculate confirmed malaria case incidence in the intervention and control clusters in Mali and Kenya. In Kenya, specific dates for data collection will be specified in the study site-specific SAP and protocol in terms of timing of data collection/analysis start after ATSB deployment (i.e., a wash-in period of ~ 2 weeks after ATSB deployment may be included and should be precisely pre-specified in Kenya site specific SAP). In Mali, facility-based assistants use electronic tablets with a custom application for collecting case data. Data will be transmitted weekly to the field data manager. In Kenya, health care data are entered into ScanForm (https://about.scanform.qed.ai/) registers at facilities and by community health workers. Individually identifiable data will not be extracted or collected by the trial staff for this outcome.

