### Secondary outcomes

1. RDT infection prevalence

Prevalence of patent malaria infection detected by RDT among participants aged 6 months and older is calculated as the number of eligible, consenting participants with positive RDT results divided by the number of eligible, consenting participants with valid RDT results, collected during the cross-sectional survey (rolling survey in Kenya).2. Passive incidence

Incidence rate of passively reported clinical malaria among participants of all ages, defined as the number of malaria confirmed cases (by RDT or microscopy), linked to study clusters by place of residence, per 1000 population per year, using routine data from health facilities with patients linked to study clusters (i.e., by name of the village of residence) and cluster population sizes for the denominator. Cluster population sizes will be calculated based on the number of HH residents identified in the cluster area (core only where possible/relevant) during the census/enumeration. Malaria-confirmed cases will include only those given a diagnosis of blood test (RDT or microscopy) confirmed malaria (ICD-10-M B50-54 and subcodes).3. Parity

The parity outcome is the non-parous proportion: the proportion of freshly caught, non-blood-fed female adult *Anopheles* spp. mosquitoes captured during human landing catch which have never been gravid (are parous) as determined by the method of Detinova (1962). The outcome is assessed in a sub-sample of clusters, houses, and nights. Data will be disaggregated by species (and/or sub-species) with species determination made by taxonomic key and PCR where necessary. Mosquitoes will be classified as parous or non-parous. Mosquitoes with inconclusive results will be excluded from the analysis of parity.4. Mosquito abundance

The number of adult *Anopheles* spp*.* captured in CDC UV light traps per night per trap. The outcome is assessed in a sub-sample of clusters, houses, and nights. Data will be disaggregated by species (and/or sub-species) with species determination made by taxonomic key and PCR where necessary. Mosquitoes with inconclusive speciation will be included in total *Anopheles* spp. abundance calculations but excluded from any species-specific analyses.5. Sporozoite rate

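### The aggregated passive-incidence analysis is a Poisson model on cluster totals with no binding allowance for between-cluster variation, so its intervals and p-values are invalid as written

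*SAP article*

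**What the plan says.** In the SAP article, section Routine clinical incidence, the passive outcome is analysed "using a generalized linear model framework with a Poisson likelihood and a log link function". The model applies at cluster level "where only aggregated data is available", and the data are reduced first: "The incidence will be summed for all months of follow-up within each study cluster". The linear predictor contains an intercept, the arm effect and log exposure, and nothing else.

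The text around the equation describes a different model. It defines the Poisson mean conditional on a cluster effect u_j and promises to report the "standard deviation or variance of the random effects distribution". Neither quantity exists in the model as written.

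The section also has an overdispersion clause. The check asks whether mean and variance agree after conditioning on cluster, and gives as its example "are the within-cluster mean and variance similar". The consequence is that "if the variance is substantially larger, a negative binomial likelihood will be considered".

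A second model, with random cluster intercepts, follows for the case where individual-level data exist. The section Passive case detection says: "Individually identifiable data will not be extracted or collected by the trial staff for this outcome".

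**The concern.** Clusters are the randomised units, and their underlying malaria rates differ for reasons unrelated to the intervention. A Poisson model on cluster totals with no cluster term counts every case as independent information on the arm effect. Its standard error then shrinks with the number of cases, whereas the real uncertainty is limited by the number of clusters (38 per arm in Mali, 35 in Kenya).

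The SAP's other Poisson regressions (primary outcome, individual-level passive incidence, mosquito abundance, human landing rate) all carry a random cluster intercept. This one does not.

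Passive incidence is a stated secondary objective, and the Multiplicity section applies no adjustment to secondary outcomes, so a spurious result could be read as supporting the primary finding. The article is also the master plan for the site-specific SAPs, so the equation can be carried into them.

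**Working it through.** **Is there a figure to reproduce?** The SAP gives no power, error rate, CV or case count for the passive outcome, so there is nothing to reproduce for it. The closest planning value is the CV of 0.40 for cohort incidence (Table 2). How the plan uses that value can be checked with the person-time formula for cluster trials:

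c = 1 + (z_α/2 + z_β)² × [(λ0 + λ1)/y + k²(λ0² + λ1²)] / (λ0 − λ1)²

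- Mali: λ0 = 0.40, λ1 = 0.28, y = 3850 × 0.8 / 76 ≈ 40.5, c = 38. Power 87.6%, against 88% stated.
- Zambia: λ0 = 0.50, λ1 = 0.35, y = 1610/70 = 23, c = 35. Power 80.4%, against 80% stated.
- Kenya: λ0 = 0.845, λ1 = 0.5915, y = 1260/70 = 18, c = 35. Power 84.0%, against 80% stated.

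Mali and Zambia reproduce with k = 0.40 and Kenya comes out higher. This confirms how 0.40 is used for the cohort. It does not show that 0.40 is right for the passive outcome.

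**Effect on the passive model.** Let m be the expected cases per cluster and k the between-cluster CV. A cluster total has variance m(1 + k²m), but the model assumes m. Hence:

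- true SE / reported SE = √(1 + k²m)
- actual two-sided type I error = 2[1 − Φ(1.96 / √(1 + k²m))]

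| k | m | SE ratio | Type I error |
|---|---|---|---|
| 0.40 | 50 | √9 = 3.0 | 51% |
| 0.40 | 200 | √33 = 5.7 | 73% |
| 0.40 | 1000 | √161 = 12.7 | 88% |
| 0.20 | 50 | √3 = 1.7 | 26% |
| 0.20 | 200 | √9 = 3.0 | 51% |
| 0.10 | 400 | √5 = 2.2 | 38% |

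At k = 0.40, type I error passes 50% when the ratio reaches 1.96/0.6745 = 2.906, that is at m = (2.906² − 1)/0.16 ≈ 47 cases per cluster.

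**Is that range of m plausible?** The Trial population section gives 100 to 400 households per cluster. Assuming 5 people per household and 0.1 to 0.4 passive cases per person-year over 2 years, m runs from 500 × 0.1 × 2 = 100 to 2000 × 0.4 × 2 = 1600. Household size and passive rate are assumptions.

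**Worked interval.** With 35 clusters per arm, m = 100 and k = 0.40, the reported SE of the log rate ratio is √(2/3500) = 0.024. The true SE is √[(2/35)(1/100 + 0.16)] = 0.099. Around an estimate of 1.00, the reported 95% interval is about 0.95 to 1.05 and the honest one about 0.82 to 1.21.

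**Simulation under no effect** (gamma cluster rates, unequal cluster sizes, 35 and 38 clusters per arm, 3000 runs per setting). At k = 0.40 the plain Poisson test rejected in 51–55% of trials at m = 50, 66–67% at m = 100, 82% at m = 400 and 89–90% at m = 1000. At k = 0.20 and m = 50 it rejected in 26–29%.

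Methods that carry between-cluster variance, at k = 0.40:

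- t-test on cluster log rates: 4.7% to 5.5%.
- Quasi-Poisson: 6.0% to 6.9%.
- Negative binomial on totals (35 per arm, 400 runs each): 7.3% at m = 100 and 5.5% at m = 400.

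**Can the safeguard be applied?** Conditioning on cluster leaves a single number per cluster. It has no within-cluster variance to compare with a mean, so the check as worded cannot be computed for aggregated data.

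**The case against.** The strongest reply is that the authors foresaw excess variance and named a negative binomial, which would largely cure the problem. Overdispersion of the size shown above would also appear in any ordinary fit check. The references to u_j and to a random-effects variance suggest a dropped term or text carried over from another section, not a decision to ignore clustering. That is a fair reading of intent. It does not make the plan sound: the check conditions on cluster both in its general statement and in its example, the switch is discretionary, and the equation and text still disagree.

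The reply on size also stands in part. The CV of 0.40 is for a cohort of children, the passive outcome covers all ages, and the case counts are assumed. Restricted randomisation may balance baseline incidence and so lower the effective CV. If it removed half the between-cluster variance (k² = 0.08), the ratio at m = 200 would be √17 = 4.1 and type I error about 64%.

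Two further inferences are tempting but not supported.

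- A reader might conclude that the random-intercept model can never apply because identifiable data are not collected. De-identified individual records are not excluded by that statement, so that branch remains open.
- A reader might also infer that cases cover core and buffer while the denominator covers the core only, since the population is "based on the number of HH residents identified in the cluster area (core only where possible/relevant"). Nowhere is the numerator said to include buffer residents, the qualifier can mean core only where cases can be placed there, and the model section takes the enumerated cluster population as exposure. A mismatch is not established.

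**Conclusion.** The point holds for the aggregated-data branch of one secondary outcome in two of the three trials. Followed as written, it gives intervals and p-values that ignore between-cluster variation, and the stated safeguard neither can be computed nor is binding.

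The size is conditional on k and m. With k = 0.40 borrowed from the cohort and 50 to 1000 cases per cluster assumed, the SE is about 3 to 13 times too small and type I error about 51% to 88%. At k = 0.20 and 50 cases it is 1.7 times and about 26%. It would go too far to say outright that a true null would usually be declared significant: this needs plain Poisson to be kept and a CV and case count towards the upper part of the range. Error stays well above 5% at every setting in the table.

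The primary and interim models, and the individual-level passive model, include random cluster intercepts and are untouched.

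**What to change.** In Routine clinical incidence, reconcile the equation with its text and name one binding default for aggregated data. Either of these would do:

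- a negative binomial, or a Poisson model with a cluster-level random intercept, on cluster totals. The negative binomial is already named in the SAP, and the random intercept matches its other Poisson models.
- a t-test on cluster log rates, stating how a zero count is handled. This is an alternative and not an equivalent, because it weights clusters equally and so estimates a somewhat different average.

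Replace the within-cluster mean–variance check for aggregated data with a between-cluster dispersion statistic given arm (for example Pearson chi-square over residual degrees of freedom). Report it descriptively and do not use it as a trigger. Carry the same wording into the Mali and Kenya SAPs.

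The cost is wording and wider intervals; no new data are needed. At k = 0.40 with 35 clusters per arm, the simulated negative binomial SE of the log rate ratio was 0.095 to 0.097, against Poisson values of 0.024 (m = 100) and 0.012 (m = 400). As an illustration, a 30% reduction (ln 0.70 = −0.357) would still lie about 0.357/0.097 = 3.7 standard errors from zero.

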### Parity

Daily female vector mosquito survival determined by parity is the main entomological outcome of the trial. The primary analysis will be conducted using parity data at the individual mosquito level with a multi-level (variance components model) constructed on a generalized linear model framework with a Bernoulli likelihood and a logit link function. Random intercepts will be included for each entomological study cluster and for each sampling household, and the study arm will be included as a fixed effect coded categorically as 0 for arm A and 1 for arm B. A simple model will first be considered as an unadjusted analysis which only includes fixed effects for study arm as described, and nested random effects for household and study cluster and an intercept. A more fully adjusted model will also be used for analysis to account for the complex sampling design by which mosquitoes are captured for parity analysis. This model will include fixed effects for collection location (indoors vs. outdoors), time since intervention, and calendar month as a seasonality adjustment. Additional random effects will be considered for the catch team/HLC individual. The models will generally take the form below where *p*_*ij*_ is the probability of parity at the individual mosquito level (*i* indexes individual mosquitoes within clusters and* j* indexes clusters), *α* is the global intercept, *X*^*arm*^_*ij*_ is the arm assignment for individual *i* in cluster *j*, *β*_*arm*_ is the arm effect to be estimated, *X*^*indoors*^_*ij*_ represents the individual mosquito being caught indoors, *β*_*indoors*_ is the effect of being indoors on parity relative to collection happening outside, *X*^*time*^_*ij*_ represents a measure of the continuous time since the start of the trial, and *β*_*time*_ is meant to capture an overarching time trend; this variable can also be interacted with the study arm fixed effect to produce an estimate of the difference in time trend by study arm. *X*^*month*^_*ij*_ represents a series of monthly dummy variables in which individual mosquitoes were caught, and *β*_*month*_ represents the series of monthly intercepts, intended to capture seasonal variation in parity. *u*_*j*_ are random intercepts for the cluster, *σ* is the standard deviation of the cluster random intercept distribution, *h*_*k*_ are random intercepts for houses, and *σ*_*h*_ is the standard deviation of the household random intercept distribution:$$\mathrm{logit}({p}_{ij})=\alpha +{X}_{ij}^{arm}{\beta }_{arm}+{X}_{ij}^{indoors}{\beta }_{indoors}+ {X}_{ij}^{time}{\beta }_{time}+\sum_{month=1}^{11}{X}_{ij}^{month}{\beta }_{month}+{u}_{j }+{h}_{k}$$

where the likelihood is of the form:$${y}_{ij}\sim Bernoulli({ p}_{ij})$$

And the random intercepts are assumed to follow a normal distribution:$${u}_{j}\sim N(0,{\sigma }^{2})$$$${h}_{k} \sim N\left(0,{\sigma }_{h}^{2}\right)$$

Model results will be presented as the estimates of *α* and the odds ratio for the arm above and the standard deviation or variance of the random effects distributions. 95% confidence intervals for the odds ratio and *α* estimates as well as *z*-statistics and *p*-values for each coefficient will be presented.

Analysis based on cluster summaries will also be considered. All parity measurements within each cluster will be summarized as a single proportion. The cluster estimates of the proportion parous will be compared across arms using Student’s *t*-test. Results will be presented as mean parity and standard deviation of parity as well as *t*-statistic and *p*-value. 95% CIs for mean parity will also be presented for each arm.

### Mosquito abundance

The analysis of data on mosquito abundance derived from capture of adult *Anopheles* spp. mosquitoes via CDC UV light traps placed indoors and outdoors near houses overnight will be constructed on a generalized linear model framework with a Poisson likelihood and a log link function. Random intercepts will be included for each entomological study cluster and study arm will be included as a fixed effect coded categorically as 0 for arm A and 1 for arm B. A simple model will first be considered an unadjusted analysis which only includes fixed effects for study arm as described, and cluster-level random effects and an intercept. Autoregressive terms may also be considered with appropriate lags determined by temporal partial auto-correlation functions. The model will take the form below where *y*_ij_ is the count of adult *Anopheles* spp. mosquitoes caught at the individual trap night (*i* indexes individual trap nights within clusters and* j* indexes clusters), *α* is the global intercept, *X*^*arm*^_*ij*_ is the arm assignment for individual *i* in cluster *j*, *β*_*arm*_ is the arm effect to be estimated, *X*^*indoors*^_*ij*_ represents the trap-night observation being indoors, *β*_*indoors*_ is the effect of being indoors on mosquito density/abundance relative to collection happening outside, *X*^*month*^_*ij*_ represents a series of monthly dummy variables in which individual mosquitoes were caught, and *β*_*month*_ represents the series of monthly intercepts. *u*_*j*_ are random intercepts for the cluster and *exposure*_*i*j_ is the number of trap nights corresponding to the particular *y*_*ij*_ observation (generally this will be equal to one (where it does equal one for all observations the log(*exposure*_*ij*_) term may be omitted)) for trap night *i* in cluster *j*, *λ*_*ij*_ refers to the *log E(y*_*ij*_*|u*_*j*_*)*, and *σ* is the standard deviation of the random intercept distribution:$$\mathrm{log}E\left({y}_{ij}|{u}_{j}\right)=\alpha +{X}_{ij}^{arm}{\beta }_{arm}+{X}_{ij}^{indoors}{\beta }_{indoors}+ \sum_{month=1}^{11}{X}_{ij}^{month}{\beta }_{month}+{u}_{j}+\mathrm{log}({exposure}_{ij})$$

where the likelihood is of the form:$${y}_{ij}\sim Pois({\lambda }_{ij})$$

And the random intercepts are assumed to follow a normal distribution:$${u}_{j}\sim N(0,{\sigma }^{2})$$

Results will be presented as the incidence rate ratio (IRR), corresponding 95% confidence interval, and *p*-value based on the *z*-statistic. This outcome will also be checked for the distributional assumption that the mean and variance of the outcome are similar after conditioning on cluster (e.g., are the within-cluster mean and variance similar); if the variance is substantially larger, a negative binomial likelihood will be considered.

